### Ancillary studies

Two ancillary studies will be conducted within the RifT trial, the second of which will only take place at Mulago Hospital.

***Evaluation of the diagnostic accuracy of Xpert MTB/Rif Ultra (Ultra) in TBM***. Our hypothesis is that CSF Ultra is significantly more sensitive than CSF Xpert MTB/Rif or culture in the diagnosis of TBM.

***Descriptive study of brain tissue rifampicin concentrations on autopsy specimens***. Our hypothesis is that brain tissue concentrations will correlate with plasma and CSF concentration and will be significantly higher in the investigational arms.

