### Interventions

***Diagnostic lumbar puncture***. At the time of screening, after informed consent has been received, a diagnostic lumbar puncture will be performed with a ~10ml CSF sample collected. The sample with then be tested with an enhanced TB diagnostic panel including Xpert MTB/Rif, Ultra, MGIT culture, Biofire meningoencephalitis multiplex polymerase chain reaction and next generation sequencing.

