### Statistical considerations

***Sample size.*** Approximately 800 adults presenting with symptoms of meningitis will be assessed, of which it is anticipated two-thirds will have cryptococcal meningitis. The circa 240 patients with negative CSF cryptococcal antigen (crAg) will undergo a comprehensive TBM diagnostic panel (Xpert MTB/Rif, Xpert Ultra, mycobacterial growth indicator tube (MGIT) culture, and/or next generation sequencing) from which we anticipate 60 people with suspected or confirmed TBM will be recruited into the randomised trial.

The sample size is determined following the assumption that PK parameters are normally distributed on the log scale. Estimated rifampicin log-transformed C
_max_ standard deviation is taken from
*Ruslami et al*.
^1^ The global study significance level (alpha) will be 10%, which is appropriate for phase II studies. Using the Bonferonni correction for multiple testing, each individual comparison will be made with alpha of 5%. Group sample sizes of n=15 achieve 90% power to reject the null hypothesis of equal means when the log-transformed population mean difference is 0.54mg/L with standard deviation of ±0.36mg/L in the control group and ±0.48mg/L (33% higher) in the experimental group, with a significance level of 0.05 using a two-sided, two sample unequal variance t-test. If the standard deviation differs from our estimate, the overall detectable effect size at 90% power will be 1.5 times the standard deviation, and 1.27 times the standard deviation at 80% power. We will not formally compare equivalence of the two investigational arms as this would require a larger sample size. Comparison of the two investigational arms will be primarily descriptive.

This phase II study would be underpowered to detect a survival benefit unless the effect size is large. A one-sided log rank test with 20 subjects per arm provides 80% power at 0.05 significance to detect a hazard ratio of 0.285 when 40% of controls survive 8-weeks. This assumes no more than 1 person drops out or is lost to follow-up per arm. The prior lost to follow up rate has been <1% in recent Ugandan meningitis trials.

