**Clinical outcomes**

Survival at 8 and 24 weeks will be calculated using the risk difference, from a generalised linear regression model adjusted for site and BMRC TBM grade. Kaplan-Meier curves will also be used to compare time to death between treatment arms, with censoring and loss to follow-up handled as previously described. Cox proportion hazards regression will be used to assess the effects of rifampicin dose, plasma/CSF rifampicin concentration, HIV, MRC severity grade and baseline GCS on survival.

When calculating time to normalization of GCS continuous-valued secondary endpoints will be compared with general linear models or Wilcoxon rank-sum tests as appropriate. Death can be considered a competing risk. χ
^2^ test will be used for comparison of proportions of patients with TBM-IRIS by intervention arm.

***Secondary analysis.*** We will explore the relationship between rifampicin exposures and clinical outcomes using a population pharmacokinetic-pharmacodynamic model. We will consider C
_max_ and AUC
_0-24h_ as the exposure variables. Survival, proportion with normalisation of conscious level and functional status (as determined by modified Rankin score) are the response variables.

***Planned subgroup analyses.*** Specified high-risk subgroups are of interest because of potential different responses to intravenous rifampicin from both an efficacy and safety perspective, and the clinical utility in future physician decision-making. With standard therapy, worse clinical outcome is associated with altered mental status, high organism burden. Subgroups of interest include:

1. TBM Diagnostic category (Definite, Probable, Possible)
^33^
2. British Medical Research Council (BMRC) TBM disease severity
^7^
3. CSF inflammation (CSF white blood cells) by tertiles4. CD4 at study entry5. ART status at study entry

***Analysis of ancillary studies.*** The results of ancillary studies will be reported separately from the main trial.

Findings of the diagnostic sub-study will be reported in line with the Standards for the Reporting of Diagnostic Accuracy studies (STARD) guidelines. Sensitivity and specificity will be calculated against a composite reference standard (any positive CSF test for
*M. tuberculosis*) and against the published uniform case definition of ‘probable’ or ‘definite’ TBM
^33^. A latent class analysis will also be performed.

The studies on brain tissue concentration at autopsy will be primarily descriptive.

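### The composite reference for the Ultra sub-study contains the tests under evaluation, so specificity against it is 100% by construction and its sensitivity contrast measures only relative positivity

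*Protocol article*

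**What the plan says.** The Ancillary studies section of the protocol article sets the aim: "Our hypothesis is that CSF Ultra is significantly more sensitive than CSF Xpert MTB/Rif or culture in the diagnosis of TBM".

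The paragraph on analysis of ancillary studies, under Statistical considerations, names three analyses:

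1. "Sensitivity and specificity will be calculated against a composite reference standard (any positive CSF test for" M. tuberculosis).
2. The same sentence continues "and against the published uniform case definition of ‘probable’ or ‘definite’ TBM".
3. The next sentence reads "A latent class analysis will also be performed".

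The section on the diagnostic lumbar puncture, under Interventions, shows which CSF tests are run. The sample goes through an "enhanced TB diagnostic panel including Xpert MTB/Rif, Ultra, MGIT culture", with multiplex PCR and sequencing listed after these. The sample size section gives the scale: "The circa 240 patients with negative CSF cryptococcal antigen (crAg) will undergo a comprehensive TBM diagnostic panel", and again lists Xpert, Ultra and culture.

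No sentence removes the index test from the composite. None says whether an Ultra result counts towards the uniform case definition, and none ties the hypothesis to one of the three analyses.

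**The concern.** A reference standard should be able to disagree with the test it judges. On a plain reading, this composite cannot disagree with a positive result on Ultra, Xpert or culture, because that result by itself makes the reference positive.

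Two things follow. First, the planned specificity against this reference carries no information: it is 100% for all three tests, however poor they are. Second, the planned sensitivity no longer separates detecting more disease from being positive more often. The hypothesis concerns greater sensitivity, and a false-positive Ultra result would count in its favour.

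At stake are an uninformative specificity shown as an estimate and a sensitivity contrast that could be read as more than it is.

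**Working it through.** The document gives no sample size, power or accuracy figure for the sub-study, so there is no stated figure to reproduce. The check has a logical part, which needs no assumption, and an illustration, which does.

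**Logic**

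Let N be the number of composite positives. For a component test, let TP and FP be its positives among true cases and true non-cases. Every positive result lies inside the composite. Hence:

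- Apparent specificity = composite-negatives that test negative / all composite-negatives = 100%, because no composite-negative patient has a positive component test.
- Apparent sensitivity = (TP + FP) / N.
- Apparent Ultra minus Xpert difference = [(TP_Ultra − TP_Xpert) + (FP_Ultra − FP_Xpert)] / N.

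The second bracket is the source of bias in the comparison. It is positive only if Ultra has more false positives than Xpert, and the same holds for culture.

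**Illustration**

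Inputs:

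- From the document: circa 240 patients undergo the panel, and 60 people with suspected or confirmed TBM are expected to be recruited.
- Assumed: 60 true cases and 180 non-cases among the 240, three tests in the composite, conditional independence, and the true accuracies in the table.

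Formula: N = 60 × [1 − product of (1 − sensitivity)] + 180 × [1 − product of specificities].

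For example, with 50% sensitivity throughout, 60 × (1 − 0.5³) = 52.5. If only Ultra has false positives, at 98% specificity, 180 × 0.02 = 3.6 are added and N = 56.1. Ultra shows (30 + 3.6)/56.1 = 59.9% and Xpert shows 30/56.1 = 53.5%.

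| True sensitivity, Ultra/Xpert/culture (%) | True specificity, Ultra/Xpert/culture (%) | N | Ultra, apparent | Xpert, apparent | Difference (true), points |
|---|---|---|---|---|---|
| 50/50/50 | 98/100/100 | 52.5 + 3.6 = 56.1 | 33.6/56.1 = 59.9% | 30/56.1 = 53.5% | 6.4 (0) |
| 50/50/50 | 97/100/100 | 52.5 + 5.4 = 57.9 | 35.4/57.9 = 61.1% | 30/57.9 = 51.8% | 9.3 (0) |
| 50/50/50 | 98/99/99 | 52.5 + 7.1 = 59.6 | 33.6/59.6 = 56.4% | 31.8/59.6 = 53.3% | 3.0 (0) |
| 50/50/50 | 98/98/98 | 52.5 + 10.6 = 63.1 | 33.6/63.1 = 53.3% | 33.6/63.1 = 53.3% | 0 (0) |
| 70/50/50 | 100/100/100 | 55.5 | 42/55.5 = 75.7% | 30/55.5 = 54.1% | 21.6 (20) |
| 70/50/50 | 98/100/100 | 55.5 + 3.6 = 59.1 | 45.6/59.1 = 77.2% | 30/59.1 = 50.8% | 26.4 (20) |
| 70/50/50 | 98/98/98 | 55.5 + 10.6 = 66.1 | 45.6/66.1 = 69.0% | 33.6/66.1 = 50.8% | 18.2 (20) |

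The apparent sensitivity ratios in the last three rows are 1.40, 1.52 and 1.36, against a true 1.40. Apparent specificity is 100% for every test in every row.

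**Taking Ultra alone out of the composite**

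Use the fifth row (70/50/50, all specificities 100%) with the reference set to Xpert or culture positive. Reference positives are 60 × (1 − 0.5²) = 45 and reference negatives are 15 + 180 = 195.

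- Ultra's sensitivity is 70%, which is correct.
- Ultra's specificity is (195 − 15 × 0.7)/195 = 94.6%, although it is truly 100%.
- Xpert and culture, still inside the reference, show 30/45 = 66.7% against a true 50%.

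This removal therefore does not give a fair head-to-head comparison.

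**The case against.** The strongest reply is that the composite is one of three planned analyses. A second specificity is planned against the uniform case definition, and the latent class analysis uses no fixed reference. The choice of lead analysis can reasonably sit in a separate analysis plan, and ancillary results are to be reported separately. This stands. A reader might infer that the sub-study cannot inform specificity at all, but the document does not support that. It does not show whether the case definition counts Ultra, so that reference can be neither cleared nor faulted here.

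A reader might also infer that the design inflates Ultra's advantage as a matter of course. That does not follow either. No figure in the document says Ultra has more false positives than Xpert or culture. Without false positives the sensitivity ratio is unbiased, and every discordant pair among true cases is already inside the composite, so a paired comparison is unaffected. With equal false-positive rates the advantage is zero or slightly understated. Nor is the problem peculiar to Ultra, since Xpert and culture have the same automatic specificity.

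The reply does not rescue specificity against the composite. That is a stated calculation with a predetermined answer, not a detail left to another document.

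**Conclusion.** The point holds in a limited form. Specificity against the any-positive composite is 100% by construction for Ultra, Xpert and culture. This rests only on the plain reading that the composite includes each index test.

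The sensitivity contrast against the composite is a contrast in positivity, and any bias in favour of Ultra is conditional. With equal true sensitivities of 50%, it is about 6 to 9 points if Ultra's specificity is 98% to 97% and its comparators are perfectly specific, about 3 points if theirs is 99% and Ultra's 98%, and 0 if all are 98%. These sizes rest on the assumed accuracies, the assumed 60/180 split and conditional independence.

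The issue is confined to the ancillary diagnostic study. The pharmacokinetic and safety endpoints are untouched.

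**What to change.** 1. Do not report specificity against the any-positive composite.
2. Keep the composite for the Ultra, Xpert and culture contrast, but call it relative positivity yield rather than sensitivity.
3. Take accuracy estimates, specificity above all, from the uniform case definition scored without the index test's own result, and from the latent class analysis already planned. State how the index test is handled in each.

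The cost is wording only, with no change to data collection. There are trade-offs. A reference that omits Ultra may score some true Ultra-only positives as false, which lowers its apparent specificity. Omitting each test in turn gives each a different denominator, so those estimates do not form a direct head-to-head comparison. The latent class model has assumptions of its own: conditional independence, if used, is doubtful for two related assays run on the same CSF. Which analysis should lead is therefore a judgement for the investigators.

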### Ethical considerations

***Confidentiality.*** Participants will be identified only by means of a coded identification number specific to each participant. All participant-related information (including CRFs, laboratory results, radiology reports etc.) will be kept strictly confidential. All records will be kept in a secure, locked location and only research staff will have access to the records. With consent, information relevant for the future HIV care will be shared with relevant HIV clinic for continuity of care and patient safety.

All computerized databases will identify participants by numeric codes only, and will be password-protected. Upon request, participant records will be made available to the study sponsor, monitors, applicable regulatory entities, including the Uganda National Council of Science and Technology, Uganda National Drug Authority, Mulago Institutional Review Board, or London School of Hygiene and Tropical Medicine.

***Consent.*** An estimated >80% of the study population will have altered mental status at initial hospital presentation. Those presenting with meningitis and altered mental status are at the greatest risk of death, and enhanced TBM therapy may have the greatest benefit for them. This hypothesis deserves testing via inclusion into the clinical trial. Secondly, as most persons with TBM present with altered mental status, in order to make results generalizable to all TBM patients, we wish to offer enrolment to all persons. Subjects unable to give informed consent due to altered mental status may have surrogate consent provided by proxy from their caregiver/next of kin.

For subjects enrolled by surrogate consent, if and when the participant regains the physical and mental capacity to give consent, information will be provided to them and written informed consent will be sought for continuation in the trial. If a patient or representative declines to give consent for continuation at this stage, his/her wishes will be respected.

A person who speaks and understands the language of the informed consent document, but does not read and write, can be enrolled in a study by "making their mark" or via a thumbprint on the informed consent document. In this event, an impartial, literate third party must witness the entire consent process and sign the informed consent document. The witness’s name, signature, and relationship must be recorded on the informed consent document. A member of the study team is not an impartial third party.

Supplementary File 1 contains the participant information sheet and consent form.

***Sample use and storage.*** Additional consent will be sought for the long-term storage of samples (including blood, spinal fluid, DNA/RNA) for use in future research. In this case, samples will be stored for the purposes of future research, unless the subject asks for them to be destroyed. Alternatively, subjects may give limited consent to the collection and testing of samples for the purposes of this research only, after which the samples will be destroyed.

***Withdrawals.*** Subjects may withdraw from the study at any time by withdrawing subject consent, and will be eligible to continue to receive TB treatment from a primary TB clinic of their choice. Subjects enrolled in the study but choosing to leave the hospital early against medical advice will continue to participate in the study if they wish. Additional phone calls by study personnel will encourage the subject to seek follow up TB care and to re-join the trial per the on-going schedule of events. Assessment of vital status will continue via telephone calls at a minimum, unless consent is completely withdrawn. Participants will be asked if they would like their accrued data to be destroyed.

***Ethical approval.*** The investigators have obtained approval from the Research Ethics Committees of the London School of Hygiene and Tropical Medicine (14388), as well as the Mulago Hospital Institutional Review Board (MHREC1260), the Uganda National Council of Science and Technology, the Ugandan National Drug Authority and Mbarara Hospital.

Any further amendments will be submitted and approved by each ethics committee.

### Publication policy

We will share results though presentations at scientific conferences and in peer-reviewed open-access journals. De-identified individual patient data will be stored on LSHTM secure data repository (LSHTM Data Compass) for patients who have given consent to data sharing at the time of enrolment.

## Discussion

Tuberculous meningitis is highly fatal despite current WHO recommended therapy, particularly in HIV-positive people, who are 2–3 times more likely to die than their HIV-negative counterparts. Recent evidence from Indonesian phase II studies suggests that significantly higher dose IV or oral rifampicin enhances CNS penetration and may reduce mortality. However, there is currently no available pharmacokinetic data on high-dose rifampicin for TBM in an HIV-positive African population. Furthermore, intravenous rifampicin is not widely available so finding a bioequivalent oral dose, that reaches target levels in the CNS, is a priority.

In this phase II study we anticipate the sample size will not be sufficient to detect small differences in mortality between the treatment arms. However, the pharmacokinetic and pharmacodynamic data will be used to define optimal rifampicin dose, and route of administration in an HIV-positive population, and this will be taken forward into a larger phase III randomised controlled trial, if safe and tolerable.

## Data availability

No data are associated with this article.
